#### Predictors

The study examines a range of predictors that may influence the primary and secondary outcomes. These predictors include demographic factors such as age, sex, ethnicity and socioeconomic status. Clinical history, including pre-existing comorbidities such as COPD, asthma, cardiovascular disease, smoking status and vaccination history, is another important predictor. Clinical presentation at the time of admission, including symptoms, severity scores such as the National Early Warning Score 2 (NEWS2)^6^ and initial laboratory and imaging findings, are also critical predictors.

By clearly defining these variables, the UNIVERSAL study aims to provide comprehensive insights into the phenotypic diversity, disease progression and economic impact of RVIs in hospitalised adults. This detailed analysis will contribute to the development of targeted interventions and improve patient outcomes

### Data sources and measurement

The UNIVERSAL study employs rigorous and standardised data collection methods to ensure consistency and reliability across multiple sites. For each variable of interest, the sources of data and methods of assessment are carefully outlined below and in online supplemental material 2. Where there are multiple groups or measurement methods, comparability is ensured through standardised protocols and training.

#### Demographic and clinical data

Demographic and clinical data are sourced from patient interviews and medical records. Detailed demographic information, including, sex, age at enrolment, height, weight, ethnicity, postcode, number of people in household and smoking history, is collected through structured patient interviews conducted by trained research staff. Medical history, including pre-existing comorbidities and vaccination history, is obtained from patient interviews and verified against medical records. Clinical presentation data, encompassing symptoms, duration of illness and severity scores such as the NEWS2 and OSCI, are documented using standardised assessment tools. Length of stay is addressed through review of clinical discharge summaries. During the discharge visit, details of treatments received during admission including time spent on intensive care or high dependency are collected from medical records. Mortality and readmission data are collected through medical records and patient interviews. While socioeconomic factors are not a primary focus of the study, participant postcodes are collected to allow for area-based deprivation analyses (eg, linkage to the Index of Multiple Deprivation).

#### Laboratory and imaging data

RVIs are confirmed using the BioFire® FilmArray® System or other PCR-based methods, with results recorded in the electronic study database. Levels of inflammatory markers, such as CRP are measured through blood tests conducted at baseline and repeated at discharge. Chest X-ray imaging data in the form of the reports issued by qualified radiologists are captured using standardised interpretation criteria.

#### Patient-reported outcomes

PROs are collected using validated questionnaires administered during follow-up visits. Symptom resolution is assessed by asking patients to report the presence and severity of symptoms at each follow-up visit through completion of the FLU-PRO-Plus.^7^ Quality of life is measured using standardised tools, such as the FLU-PRO-Plus and EQ-5D-5L,^8^ to capture the patient’s perspective on their recovery. Once discharged from hospital, recovery is assessed using standardised questionnaires, listed in table 2, for symptom severity, quality of life, fatigue, depression and anxiety. This provides a comprehensive and holistic approach to monitoring patient recovery, the importance of which has been highlighted following the SARS-CoV-2 pandemic. Details of the PROs used as part of the UNIVERSAL study are provided in table 2.

**Table 2 T2:** Patient-reported outcomes (PROs) in the UNIVERSAL study

PRO	Variable	Format	Reference
FLU-PRO-Plus	Symptom severity and resolution in viral illness	Assesses severity of symptoms in viral illness using 32 items across six body systems scored on a five-point severity scale based on recall of the previous 24 hours. Additional questions include loss of taste and smell.Provides a total score and individual body system scores of symptom severity and recovery over time.	^7^
EQ-5D-5L	Functional health status and quality of life (QoL)	Health status is assessed across five dimensions—mobility, self-care, usual activities, pain and anxiety/depression with five levels of severity in each dimension. A visual analogue scale rates health from 0 (worst health imaginable) to 100 (best health imaginable).	^8^
PHQ-9	Depression	Assesses for depressive symptoms and tracks changes over time. Consists of nine questions, corresponding to the 9 DSM-IV criteria for depressive disorders. Responses to each question are scored using a four-point severity scale 0 (not at all) to 3 (nearly every day). The combined total score indicates the severity of depression.	^14^
GAD-7	Anxiety	Measures the severity of generalised anxiety. Consists of seven questions that assess frequency of anxiety-related symptoms over the previous 2 weeks. Responses to each question are scored using a four-point severity scale 0 (not at all) to 3 (nearly every day). The combined total score indicated the severity of anxiety.	^15^
FACIT-Fatigue scale	Fatigue	A component of the Functional Assessment of Chronic Illness Therapy (FACIT) measurement system designed to assess the level of fatigue experienced by individuals, particularly those with chronic illnesses. It evaluates the impact of fatigue on QoL. The scale consists of 13 items addressing aspects of fatigue over the previous 1 week. Each item is rated on a 5-point Likert scale. The scores are summed with higher scores indicating less fatigue and better functional status.	^16^

The UNIVERSAL Study collects a variety of patient-reported outcomes (PROs) at multiple timepoints, from admission to 6 months post-discharge, to objectively assess symptoms and health-related quality of life (QoL). This table provides an overview of the PROs used in the study, including the specific variables they assess, their formats and the relevant references for each outcome measure.

EQ-5D-5L, EuroQol 5-Dimension 5-Level; FACIT, Functional Assessment of Chronic Illness Therapy—Fatigue Scale; FLU-PRO-Plus, inFLUenza Patient-Reported Outcome Plus; GAD-7, Generalised Anxiety Disorder-7; PHQ-9, Patient Health Questionnaire-9; UNIVERSAL, Understanding Infection, Viral Exacerbation and Respiratory Symptoms at Admission-Longitudinal.

#### Economic data

Economic data are sourced from healthcare utilisation records and patient interviews. Direct costs are obtained from HRG codes, while indirect costs, such as time off work or education, are estimated through patient interviews and self-reported data.

#### Data management

Participant data are collected at individual recruitment centres and retained in accordance with current data protection regulations. Participant data are pseudo-anonymised by assigning participant identifier codes used to identify the participant during the study and to facilitate participant-related clarification between sites and Southampton Clinical Trials Unit (SCTU). Each individual site retains a participant identification code list which is only available to site staff.

Data are entered onto a secure centralised electronic database as per an electronic case report form only by trained personnel with specific authorisation to access study data. Research data are stored in an anonymised format under the participant identifier number so that participants are not identifiable, and confidentiality is maintained. Any data collected as part of the trial will be securely stored in line with the Data Protection Act and General Data Protection Regulations.

The study database is monitored and audited continuously by a data management team at the SCTU. A data management plan (DMP) outlines the study-specific data management strategy. Central monitoring of study activities and milestones is overseen by the SCTU. Data are checked for missing or inconsistent values, and any discrepancies are raised as queries with individual sites electronically. Sites then respond to queries to resolve the discrepancies, and appropriate amendments are made on the study database. In this way, missing or incomplete data items are identified promptly to ensure data quality and completeness. The SCTU facilitates the collection of the PROs at study timepoints (weeks 1, 2, 4, 8, 12 and 26) either electronically or by postage of paper forms as per participant preference. Follow-up visits at weeks 6, 12 and 26 are carried out via telephone by trained research staff at individual recruitment centres, and data are entered onto the study database.

Once the participant has completed the study procedures after 6 months, the end of study form is completed. At the end of the study, when all participants have completed 6 months follow-up and all data queries have been resolved, the database will be frozen, and data archived according to SCTU policy.

### Bias

To mitigate potential sources of bias in the UNIVERSAL study, several strategies are employed. Standardised protocols for data collection and measurement are used across all participating sites, ensuring consistency and reliability of the collected data. All research staff undergo training to adhere to these protocols, which helps minimise variability in the data collection procedures. Additionally, quality control checks and audits are conducted to identify and correct any discrepancies or errors. This includes reviewing data for completeness and accuracy, as well as cross-verifying information from different sources.

A centralised electronic database with secure access is used to maintain data integrity and confidentiality. Efforts are also made to minimise selection bias by ensuring a broad and representative sample of the patient population from diverse urban and rural settings. Moreover, the study employs rigorous inclusion and exclusion criteria to ensure that the patient population is well-defined and comparable across sites.

### Study size

The study size for the UNIVERSAL study was determined based on several considerations. Based on previous studies, a sample size of 1000 patients is believed to provide sufficient power to detect significant differences in primary outcomes. This calculation was based on expected variability in outcomes based on previous studies.^4 9 10^ The sample size aims to ensure that the findings are statistically robust and clinically meaningful. By recruiting a large cohort across multiple geographical UK hospital sites, the study seeks to achieve comprehensive and generalisable results that can inform clinical practice and policy decisions. The sample size calculation also considered potential dropouts and loss to follow-up, ensuring that the final dataset remains sufficiently powered for detailed analyses.

### Sample size calculation

Based on previous studies and expected variability in outcomes, a sample size of 1000 patients is estimated to provide sufficient power to detect significant differences in primary outcomes for the most prevalent respiratory viruses.^9 10^ In terms of descriptive statistics on the incidence/prevalence rates, 1000/2000 participants would conservatively allow the estimation with a 95% CI of ±3.1%/2.2%. There is little consensus in the literature on how best to calculate a formal sample size for cluster analysis such as latent class modelling. Simulation studies have suggested that sample sizes in the order of 500–1000 participants are usually sufficient even in the presence of weak class-indicator associations for 80% power or greater.^9 10^ To develop a clinical prediction model of progression of illness, a minimum sample size of 932 would be required. This assumes that for a model to be useful, it would need to have an area under the receiver operating characteristic (ROC) curve of at least 0.85 and is based on an outcome prevalence of 10% and up to 18 parameters in the final model.

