## Methods and design

### Study design

The UNIVERSAL study is a multicentre, prospective, longitudinal, observational cohort study conducted across multiple secondary care hospitals in the UK. This multicentre approach allows the study to capture diverse patient demographics reflective of various geographic regions and healthcare settings across the UK. Participant enrolment began on 31 August 2022, with a target of 1000 RVI positive participants, and a planned end date of December 2025.

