### Statistical methods

A detailed statistical analysis plan has been designed for the UNIVERSAL study involving all statistical considerations to ensure robust and reliable results. Here, we will only describe the essential statistical methods for the primary analysis. For analysis involving multiple comparisons, we will adjust them with Bonferroni correction. SAS V.9.4 or above, STATA V.18 or above and R V.4.4 or above will be used for analyses.

Descriptive statistics will be used to summarise baseline characteristics, clinical presentation and outcomes related to different viral pathogens. Measures of central tendency (mean, median) and dispersion (SD, IQR) will be calculated for continuous variables, while frequencies and percentages are used for categorical variables. Univariate analyses will be used to explore the relationship between key characteristics and the outcome measures. Clustering techniques will be used to explore similar patterns with respect to symptoms, severity and duration.

Multivariable regression models will be employed to identify associations between key predictors and outcomes while controlling for potential confounders. These models will be adjusted for demographic factors (age, sex, ethnicity, socioeconomic status, vaccination status), clinical variables (severity scores, comorbidities) and treatment regimens. Prior to model fitting, multicollinearity among covariates will be assessed using appropriate statistical methods (eg, variance inflation factor), and adjustments will be made if necessary to ensure model stability. The choice of regression model (eg, logistic regression for binary outcomes, linear regression for continuous outcomes) depends on the nature of the dependent variable. For analysis involving data at multiple time points, multilevel regression with first-level autoregressive error correlation structure (ie, AR(1)) will be used to control for within-subject correlation.

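### The minimum of 932 is valid only if 18 counts all candidate parameters, but the protocol attaches 18 to the final model

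*Protocol article*

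**What the plan says.** The Sample size calculation section of the protocol article states that, for a clinical prediction model of progression, "a minimum sample size of 932 would be required". It gives three inputs. A useful model would need an "area under the receiver operating characteristic (ROC) curve of at least 0.85", and the calculation "is based on an outcome prevalence of 10% and up to 18 parameters in the final model". It names neither a formula nor a shrinkage target. The Study design section describes recruitment "with a target of 1000 RVI positive participants".

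The predictors are described in open-ended terms. The Predictors section says: "These predictors include demographic factors such as age, sex, ethnicity and socioeconomic status". It adds "pre-existing comorbidities such as COPD, asthma, cardiovascular disease, smoking status and vaccination history", then symptoms, NEWS2, and initial laboratory and imaging findings. The Primary outcomes section adds viral load and CRP. The Subgroup and interaction analyses section plans interaction terms and gives age by comorbidities as an example. The article does not say which of these are candidates for the progression model, how they are coded, or how the final parameters are chosen.

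**The concern.** Overfitting is driven by the number of parameters the data are allowed to choose among: all dummy levels, non-linear terms and interactions examined, whether or not they are kept. The sample size criterion that produces 932 therefore takes the candidate count as its input. A calculation tied to the final model would let an analyst examine any number of predictors, keep 18, and still cite 932 as sufficient.

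In that case the model would be more overfitted than the calculation implies. Its apparent AUC would be optimistic and its predicted risks too extreme. Predictors of disease progression are among the primary endpoints in the Abstract, so the number carries weight.

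**Working it through.** **Inputs from the Sample size calculation section:** AUC 0.85, outcome prevalence 10%, P = 18, stated result 932. **Planned N:** 1000 (Study design). **Assumed, because not stated:** shrinkage target S = 0.9 (the conventional default) and a normally distributed linear predictor with equal variance in patients with and without the outcome.

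**Step 1: AUC to Cox-Snell R².** The separation between the two groups is μ = √2 · Φ⁻¹(0.85) ≈ 1.466. With prevalence 0.10 the model is logit(p) = ln(0.1/0.9) − μ²/2 + μx. Integrating the log-likelihood numerically gives R² = 0.1576, against a maximum possible R² of 0.478.

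**Step 2: reproduce 932.** The shrinkage criterion is n = P / [(S − 1) · ln(1 − R²/S)].
- ln(1 − 0.1576/0.9) = −0.1925, so the denominator is 0.01925.
- n = 18 / 0.01925 = 935 (936 rounded up).
- Taking R² from three simulated data sets of 1,000,000 gives 930 to 937.

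The other usual criteria are not binding: optimism in R² of at most 0.05 needs 683, and estimating overall risk to within 0.05 needs 139. The stated 932 lies inside the simulation range, which supports both assumptions. It is reproduced with 18 entered as the candidate count.

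**Step 3: cost per candidate.** 1 / 0.01925 ≈ 52 patients. The ceiling at N = 1000 is 1000 × 0.01925 = 19.2, so 19 candidates. If 10% of patients could not be used (an assumption), N = 900 supports about 17.

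| Candidate parameters | Required n (S = 0.9) | Expected shrinkage at N = 1000 |
|---|---|---|
| 18 | 936 | 0.906 |
| 19 | 988 | – |
| 20 | 1040 | 0.897 |
| 24 | 1247 | – |
| 25 | 1299 | 0.874 |
| 30 | 1559 | 0.853 |
| 40 | 2079 | 0.814 |

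**Step 4: how many candidates might there be?** This depends on coding, which is assumed here.
- One parameter per named item (age, sex, ethnicity, socioeconomic status, COPD, asthma, cardiovascular disease, smoking, vaccination, symptoms, NEWS2, CRP, imaging, viral load): 14, needing 728.
- Ethnicity in 5 groups (+3) and smoking in 3 levels (+1): 18, needing 936.
- Virus type in 6 groups (+5) and one age-by-comorbidity term (+1): 24, needing 1247.

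**Step 5: dependence on AUC.** At AUC 0.80 and prevalence 10%, R² = 0.1115 and the denominator is 0.01323. Then 18 parameters need 18 / 0.01323 ≈ 1361, and N = 1000 supports 13.

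**The case against.** The strongest reply is that nothing has been miscalculated. The number follows from the stated inputs. If the model is pre-specified and fitted in full, candidate and final parameters coincide and 932 is right. The article describes no selection step. Its statement that "Univariate analyses will be used to explore the relationship between key characteristics and the outcome measures" does not say that those analyses screen predictors for the model. The detailed candidate list and modelling strategy also belong in the statistical analysis plan, which the article says exists. All of this stands, and it makes any shortfall conditional. It does not rescue the wording, because the article does state the input to its own calculation and attaches it to the wrong quantity.

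Three stronger readings are tempting, and the document does not support them.

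- *That 1000 patients cannot support the listed predictors.* The Predictors section covers primary and secondary outcomes in general, and nothing says that every item enters the progression model. The barest codings fit within 1000.
- *That the dropout statement is wrong.* The Study size section says "The sample size calculation also considered potential dropouts and loss to follow-up" and gives no rate. The 68 patients between 932 and 1000 (6.8%) do not contradict it, and if progression is an in-hospital outcome, later attrition matters little.
- *That using AUC 0.85 is an error.* Sizing at the level below which a model is held not to be useful is coherent. It only means that the figure depends on that level being reached.

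**Conclusion.** The point holds as an error of definition in a figure that the design relies on. The minimum of 932 is valid for 18 candidate parameters and not for 18 parameters that survive a search. At 1000 patients the ceiling is 19 candidates, about 52 patients each. If 24 are considered, the need is about 1247. If 30 are considered, it is about 1559, and expected shrinkage at 1000 is 0.85 against 0.90.

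Whether the ceiling is exceeded cannot be settled from the protocol. Plausible codings run from 14 to about 24 parameters, and more if several symptoms or laboratory values enter separately. The conclusion rests on the inferred shrinkage target of 0.9 and the normal linear predictor, both supported by the close match to 932, and on a true AUC of 0.85. This is a correction of moderate weight, not a demonstrated shortfall in the study size.

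**What to change.** In the Sample size calculation section, replace the reference to the final model with *candidate parameters considered, counting all levels, non-linear terms and interactions*. Then:

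1. List the candidates for the progression model in advance and cap them at 19 for N = 1000. The cap assumes that all 1000 patients contribute; it is about 17 if only 900 do.
2. If a wider list is kept, fit the model by penalised regression and report the optimism-corrected AUC and calibration slope.
3. State that 932 holds only if the model reaches an AUC of 0.85, and that 18 parameters would need about 1361 at an AUC of 0.80.

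The cost is a change of wording and either a shorter candidate list or a little more analysis. No extra patients are required, and the dropout statement in the Study size section can stay as it is.

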### Statistical methods

A detailed statistical analysis plan has been designed for the UNIVERSAL study involving all statistical considerations to ensure robust and reliable results. Here, we will only describe the essential statistical methods for the primary analysis. For analysis involving multiple comparisons, we will adjust them with Bonferroni correction. SAS V.9.4 or above, STATA V.18 or above and R V.4.4 or above will be used for analyses.

Descriptive statistics will be used to summarise baseline characteristics, clinical presentation and outcomes related to different viral pathogens. Measures of central tendency (mean, median) and dispersion (SD, IQR) will be calculated for continuous variables, while frequencies and percentages are used for categorical variables. Univariate analyses will be used to explore the relationship between key characteristics and the outcome measures. Clustering techniques will be used to explore similar patterns with respect to symptoms, severity and duration.

Multivariable regression models will be employed to identify associations between key predictors and outcomes while controlling for potential confounders. These models will be adjusted for demographic factors (age, sex, ethnicity, socioeconomic status, vaccination status), clinical variables (severity scores, comorbidities) and treatment regimens. Prior to model fitting, multicollinearity among covariates will be assessed using appropriate statistical methods (eg, variance inflation factor), and adjustments will be made if necessary to ensure model stability. The choice of regression model (eg, logistic regression for binary outcomes, linear regression for continuous outcomes) depends on the nature of the dependent variable. For analysis involving data at multiple time points, multilevel regression with first-level autoregressive error correlation structure (ie, AR(1)) will be used to control for within-subject correlation.

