### Variables

#### Primary outcomes

The primary outcomes of the UNIVERSAL study are focused on characterising the clinical impact of RVIs in hospitalised adults. This includes not only documenting the occurrence of various respiratory viruses, including influenza, RSV and SARS-CoV-2, but also a broader range of viruses such as rhinoviruses, parainfluenza viruses and human metapneumovirus. The study aims to evaluate their association with disease severity, progression and recovery. The study also aims to identify clinical and biological predictors of these outcomes, including markers such as viral load, inflammatory markers such as C reactive protein (CRP) and patient demographics. Another key outcome is measuring the duration of hospital stay for patients with RVIs and understanding the factors that contribute to prolonged hospitalisation.

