#### Subgroup and interaction analyses

Subgroup analyses are conducted to explore differences in primary and secondary outcomes among specific patient groups, such as those with different respiratory viruses (eg, influenza, RSV, SARS-CoV-2) or varying severity levels. Interaction terms are included in regression models to examine potential interactions between key variables, such as the interaction between age and comorbidities in predicting disease severity. We will also consider stratifying the analysis by different respiratory viruses if the sample size allows. These analyses help identify variations in treatment effects and outcomes across different subpopulations.

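### Bonferroni is fixed for multiple comparisons, although Holm's step-down procedure gives the same familywise guarantee and never rejects fewer hypotheses, so some power may be given up

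*Protocol article*

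**What the plan says.** The Statistical methods section of the protocol article states the multiplicity rule in one sentence: "For analysis involving multiple comparisons, we will adjust them with Bonferroni correction". It attaches no condition, names no step-down variant and gives no reason for the choice. Just before this, the section limits its own scope: "Here, we will only describe the essential statistical methods for the primary analysis". It also refers to a detailed statistical analysis plan, which is not shown.

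Several comparisons are in prospect. The Primary outcomes section covers a list of viruses, "including influenza, RSV and SARS-CoV-2, but also a broader range of viruses such as rhinoviruses, parainfluenza viruses and human metapneumovirus", and their association with severity, progression and recovery. The Subgroup and interaction analyses section adds groups "such as those with different respiratory viruses (eg, influenza, RSV, SARS-CoV-2) or varying severity levels". The Sample size calculation section claims that "a sample size of 1000 patients is estimated to provide sufficient power to detect significant differences in primary outcomes for the most prevalent respiratory viruses", but attaches no power figure, effect size or adjusted significance level to that claim.

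**The concern.** The point is not an omission that the analysis plan might fill. The article makes a positive choice, and another method improves on it for the same purpose. If the aim is to hold the familywise error at 5% and find as many real differences as possible, Holm does at least as well as Bonferroni on every data set, with no extra assumption.

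What may be lost is the second and later findings in a family. That matters in a study whose main aim is to describe how viruses and patient types differ, because several real differences within one family are then plausible.

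**Working it through.** **The article's own figures.** None depends on the multiplicity method, and they reproduce.
- Precision: the article says "1000/2000 participants would conservatively allow the estimation with a 95% CI of ±3.1%/2.2" (per cent). The half-width is 1.96 × √(0.25/n), which is 3.10% for n = 1000 and 2.19% for n = 2000.
- Prediction model: "a minimum sample size of 932 would be required", with an area under the curve of "at least 0.85 and is based on an outcome prevalence of 10% and up to 18 parameters in the final model". The shrinkage criterion is n = p / [(S − 1) ln(1 − R²/S)]. Take p = 18, S = 0.9 (assumed) and Cox-Snell R² = 0.158, derived from an area of 0.85 and a prevalence of 10%. This gives 932. With R² unrounded (0.1576) it gives 935.

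**Why Holm cannot do worse on rejections.** For m tests, Bonferroni compares every p-value with α/m. Holm compares the ordered p-values with α/m, α/(m − 1), …, α and stops at the first failure. For m = 3 and α = 0.05 the thresholds are 0.0167 each for Bonferroni, and 0.0167, 0.025 and 0.05 for Holm. Each Holm threshold is at least α/m, so every Bonferroni rejection is also a Holm rejection. The first threshold is the same, so the chance of at least one rejection is the same.

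**Inputs for the size of the gain (all assumed, because the article does not give them).**
- Two-sided familywise α of 0.05, in line with the 95% intervals.
- Family size m = 3 (pairs among the three viruses named for subgroups), 15 (6 × 5/2 pairs among six named viruses), and 6 and 10 between these.
- Each real difference has 80% power before adjustment, that is, a standardised effect of 1.960 + 0.842 = 2.802.
- Tests are simulated as independent or with correlation 0.5, not as exact pairwise contrasts. There are 100,000 replicates per scenario.

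**Check of the Bonferroni column.** Power is Φ(2.802 − z), where z is the two-sided critical value at 0.05/m. For m = 3, z = 2.394 and power is Φ(0.408) = 66%. For m = 10, z = 2.807 and power is Φ(−0.005) = 50%. Both agree with the simulation.

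**Average power per real difference, Bonferroni to Holm, independent tests:**

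| m | one real | about half real | all real |
|---|---|---|---|
| 3 | 66.0% to 66.2% | (one real) | 65.9% to 75.1% |
| 6 | 56.4% to 56.5% | 56.5% to 59.7% | 56.5% to 68.2% |
| 10 | 49.6% to 49.7% | 49.8% to 53.0% | 49.8% to 60.9% |
| 15 | 44.7% to 44.8% | 44.8% to 47.4% | 44.7% to 54.2% |

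With correlation 0.5 and all differences real, the result for m = 3 is 66.0% to 73.6%, and for m = 10 it is 49.8% to 60.7%. The power to detect every difference, when all are real and tests are independent, rises from 28.3% to 49.3% for m = 3 and from 3.2% to 21.9% for m = 6.

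**Larger effects (independent tests, 200,000 replicates).**
- 10 tests, effect 3.0: Bonferroni 57.7%; Holm 57.8% with one real, 61.4% with five and 65.8% with eight.
- 10 tests, effect 3.5: Bonferroni 75.6%; Holm 75.7% with one real, 79.4% with five and 83.9% with eight.
- 6 tests, effect 3.5, five real: 80.6% to 88.0%.
- 10 tests with two or three real: gains of about 0.8 and 1.7 points.

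**Error control.** With no real difference, familywise error is identical for the two methods (0.048 to 0.050, independent tests). With some real differences, Holm's largest value in the first set of scenarios was 0.047. With 8 of 10 real at effect 3.5, it was 1.0% for Bonferroni and 3.4% for Holm. In no replicate of the first set did Holm reject fewer hypotheses.

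**The case against.** The strongest reply is that nothing here is wrong. Bonferroni controls the familywise error, no stated figure depends on it, and replacing one valid method with a somewhat stronger one comes close to preference. This stands as a limit on the weight of the point. It does not remove the point, because the article commits to the weaker method and offers no reason for it.

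A second reply concerns intervals. Bonferroni gives simultaneous intervals that match its adjusted p-values. Holm has no equally simple counterpart, so a comparison may be significant by Holm while its Bonferroni-width interval includes the null value. For a largely descriptive cohort that is a fair trade-off. It is small, and the article does not cite it.

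Third, Holm's extra rejections include a few more false ones. Both methods respect the 5% bound, but the realised error is higher with Holm. Bonferroni also bounds the expected number of false rejections at α, which Holm does not: with 10 null tests, Holm gave 0.053 at correlation 0.5 and 0.063 at 0.8, against at most 0.050. Holm's advantage therefore holds for familywise control and power, not for every error measure.

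A reader might also infer that every multiple comparison in the study, including each predictor coefficient, will be Bonferroni-adjusted. The article does not say so. The section is confined to essential methods for the primary analysis, and the families are not defined there.

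**Conclusion.** The point holds as a low-priority improvement. Bonferroni is valid, and Holm offers the same familywise guarantee with equal or greater power. Under the stated assumptions the gain in average power is about 0 points if one difference is real, about 2 to 4 points if 3 to 5 of 10 are real, and about 7 to 12 points if most or all are real. The chance of at least one finding is unaffected. The article does not fix the number of comparisons, alpha or effect sizes, so these figures are a range and not an estimate for this study.

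It would be tempting to conclude that real associations will be missed, or that the study is underpowered because of Bonferroni. The document supports neither. Differences may be missed, depending on how many are real, and no power figure is given that the adjustment could overturn.

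**What to change.** In the Statistical methods section, replace the words *Bonferroni correction* with *Holm step-down adjustment (familywise 5%)* and report Holm-adjusted p-values. Where simultaneous intervals are wanted, keep Bonferroni-width intervals and note that they can be more conservative than the adjusted p-values. If matching intervals are the reason for Bonferroni, the alternative is to keep it and say so.

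The change needs no new data, participants or assumptions: it is a wording change and a software option. The cost is the occasional mismatch between interval and p-value, and a realised familywise error closer to its 5% limit. The ±3.1%/2.2% precision figures, the minimum of 932 and the target of 1000 stay as they are.
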